#### Control group (CO)

CO receives general care. Participants of the control group may attend other offers of the health insurance company. Interventions are not restricted. However physical activity along the study period is monitored via self-administered questionnaires.

### Collection points (Fig. 5)

**Fig. 5 Fig5:**
[figure not shown]
Collection points and outcome measures. Figure legend: t = collection point, m = minus. 0, 3, 6, 12, 24 = month of collection point related to baseline (t0)

Participants will be assessed at baseline (t0) and after (t3) the 11-week intervention period. Three follow-ups are conducted by mail 3 (t6), 6 (t12) and 21 (t24) months after the end of the intervention period. Economic evaluation will further compare data 6 (tm6), 12 (tm12), 18 (tm18) and 24 (tm24) months retrospectively (m = minus) prior to t0.

### Outcome measures (Table 4, Fig. 5)

**Table 4 Tab4:** Outcome measures

Characteristics & confounders	Description and instrument	Data source	Sample	Collection points
Patient’s characteristics	Date of birth, gender, ethnicity, BMI (height, weight), site (s) of OA diagnosis, date of first OA diagnosis, labour situation (working, retired, unemployed, in rehabilitation status)	SAQ, IDB	IG, CO	t0, t3, t6, t12, t24
Primary outcome measure	Clinical Outcomes			
Pain	WOMAC Index 3.1 German (11-box NRS): subscale pain	SAQ	IG, CO	t0, t3
Function	WOMAC Index 3.1 German (11-box NRS): subscale physical functioning	SAQ	IG, CO	t0, t3
Secondary outcome measures	Clinical Outcomes		IG, CO	
Stiffness, disease specific impairment	WOMAC Index 3.1 German (11-box NRS): subscale stiffness, overall score	SAQ	IG, CO	t0, t3, t6, t12, t24
Pain, physical function	WOMAC Index 3.1 German (11-box NRS): subscale pain, subscale physical function	SAQ	IG, CO	t6, t12, t24
Health related quality of life	VR-12 incl. VR-6D utility index (4-week-time-slot)	SAQ	IG, CO	t0, t3, t6, t12, t24
General Self-Efficacy	General self-efficacy scale (GSE)	SAQ	IG, CO	t0, t3, t6, t12, t24
Response to exercise	Omeract-OARSI Set of Responder Criteria: composite score with minimum absolute and relative change levels for pain or pain & function	SAQ	IG, CO	t0, t3, t6, t12, t24
Physical activity status	Habitual physical and sports activity status	SAQ	IG, CO	t0, t3, t6, t12, t24
Time to surgery	Endpoint “elective joint replacement”	IDB	IG, CO	t0, t3, t6, t12, t24
	Patient satisfaction			
	Modified version of the ZUF-8 Questionnaire to assess patient satisfaction	SAQ	IG	t3
	Economic data			
Unspecific and specific (OA-related) health care costs	Out-patient costs, hospital costs, costs related to drugs, adjuvants and physical modalities, rehabilitation costs, sick-pay	IDB	IG, CO	tm24, tm18, tm12, tm6 t0, t3, t6, t12, t24
Unspecific/specific (OA related) periods of disability	Days of disability (overall and related to OA)	IDB	IG, CO	tm24, tm18, tm12, tm6 t0, t3, t6, t12, t24
Intervention related costs	Costs for human and physical resources/session	IDB	IG	t3, t6, t12, t24
	Adherence to exercise			
Training adherence	Summarized number of attended training sessions according to training log	SAQ	IG	t3
	Safety evaluation			
Adverse events and side-effects	Summarized number and details of adverse events and side-effects according to training log	SAQ	IG	t3

Data Source: Self-administered questionnaire via postal mailing (SAQ), insurance data base (IDB). Sample: Participants of the intervention group (IG), matched pairs control group (CO)

Annotation: Unless otherwise stated, measures are conducted at baseline and at all follow-ups.

The Western Ontario McMasters Universities Osteoarthritis Index (WOMAC® NRS 3.1 German Index) is a disease-specific instrument used to evaluate self-reported *pain*, *stiffness* and *functional impairment*. It is a valid, reliable and responsive score, easy to complete, simple to score and available in multiple language forms and scaling formats [24]. The scales will be transformed into values from zero (no limitation) to 100 (maximum limitation).

The OMERACT-OARSI Set of Responder Criteria is a composite score with minimum absolute and relative change levels for pain or pain & function. Input variables for pain and function will be derived from the WOMAC Subscales *pain* and *functional impairment* [25].

The VR-12 is an open access version of the SF-12 [26]. It comprises 8 different scales, four of them related to physical health (*physical functioning, role-physical, bodily pain, general health*), and four of them related to mental health (*vitality, social functioning, role-emotional, mental health*). The VR-6D is a utility measure derived from the VR-12. The 4 week time-slot will be used for analysis.

General self-efficacy will be measured with the German version of the General Self-Efficacy scale (GSE) with a four-point Likert scale (“not right” versus “definitely right”). Ten items are designed to tap this construct. Each item refers to successful coping and implies an internal-stable attribution of success. The scale ranges from 10 to 40 points with 40 points indicating maximum self-efficacy [27].

Habitual physical activity status will be quantified with regard to sports activities as well as physical activities in everyday life. Questions are similar to those being used in the German Health Update 2012 [28, 29].

Patient satisfaction (IG only, t3) will be quantified by participants of the IG with a four point Likert scale using a modified and shortened version of the ZUF-8 [30, 31]. Modifications were made in order to adapt the eight item instrument to the outpatient setting.Patient characteristicsBody Mass Index (BMI), site (s) of OA joint diagnosis, artificial joint replacement (hip or knee and time of event).Safety evaluation (IG only, t3)Description of adverse events within the previous 11-week intervention period including frequency, intensity and duration of exercise related pain and possible reasons. Participants get a training log for home-based exercises where they are asked to report adherence as well as exercise related adverse events. In this way summarized data can be provided by the participants at the end of the intervention period by reviewing the training logs. Aside from this study-related safety report, patients are urged to contact their personal trainers or physicians in case of adverse events and side-effects.Adherence to exercise (IG only, t3)Number of attended training sessions (group and home-based exercises). In case of omitted sessions: Reasons for non-compliance.Socio-demographic data (insurance data base)The following socio-demographic data will be readout of the data base: date of birth, gender and labor situation (working, retired, unemployed, in rehabilitation status), complexity of work (from 1 = low to 4 = high), level of education (1 = no graduation to 4 = High School), highest level of educational attainment (from 1 = no qualification to 6 = doctoral degree), contractual form (permanent/fixed term contract, full time/part time).Economic data (insurance data base)Patient-specific economic data comprise (1) unspecific and (2) specific osteoarthritis related health care costs for the diagnosis of hip and/or knee OA, (3) Specific and unspecific days of disability and (4) intervention related costs for the exercise program:(1) Unspecific health care costs (overall costs): Sick-pay, hospital costs, out-patient costs, rehabilitation costs and costs related to drugs, physical modalities and adjuvants.(2) Specific diagnosis (hip and knee OA) related health care costs: Sick-pay, hospital costs, out-patient costs, rehabilitation costs and costs related to disease related drugs, physical modalities and adjuvants.(3) Specific (hip and knee OA related) and unspecific days of disability.(4) Intervention related costs include human and physical resources that are required for the institutional exercise sessions. Intervention related costs will be added to the above mentioned diagnosis related costs for all participants of the intervention groups according to the number of their scheduled training session (8 units).

### Statistics

#### Sample size

Below are given details on the sample size estimation for primary clinical outcomes. However, aside from statistical power, a sufficiently large sample is necessary to obtain representative results for the general population and to allow sustainable statements on the effectiveness and efficiency of the intervention for secondary clinical as well as economic outcomes. We therefore plan to include all eligible patients willing to participate in the study and finally assume a number of n = 700 in each group. This number takes into consideration the degree of capacity utilization of hip and knee training courses as well as the number of subjects non eligible due to inclusion- and exclusion criteria as well as subjects refusing consent to participate in the study (Fig. 1).

The empirical basis of the sample size estimation for primary outcomes was retrieved from the paper by Krauss et al. [17]. In this randomized controlled trial (RCT), intra-individual differences of WOMAC subscale pain and WOMAC subscale physical function identically showed an effect size of about 0.5 between the intervention and the control group (pain, intervention: −8.5 ± 13.9, control: −1.3 ± 15.3, physical function, intervention: −8.4 ± 13.4, control: −2.1 ± 12.9).

Based on the previous results of the RCT and the so-called efficacy-effectiveness gap between RCTs and studies under real life conditions [32] we finally assume an effect size of ES = 0.3.

Due to the fact that we want to test the two endpoints (pain and physical function) simultaneously and without hierarchical order, we choose a level of significance of 0.025 (two-sided, Bonferroni correction) and a power of 0.90. This leads to a sample size of 278 subjects per group in the parallel group design without cluster effects (nquery release 7.0). The drop-out rate in the intervention group of the above mentioned RCT was 8 % [17]. As this value is quite low, we assume a somewhat higher number of non-finishers and estimate the rate to be 20 %. Thus 350 subjects should be allocated to each treatment arm.

However, in our study, cluster effects may appear for subjects within identical training groups: We expect 700 included subjects participating in 170 different training courses. Thus four participants of each training group will averagely be subjects of the study (whereas the rest of the group participants are no study subjects). With a rather high intra class correlation of 0.33 we obtain a variance inflation factor of 2 for the intervention. Therefore, with 700 subjects per study arm the aimed power should be reached.

We refrain from analyzing our data using a matched-pair design as propensity score matching does not guarantee that individual pairs will be well-matched on the full set of covariates, only that groups of individuals with similar propensity scores will have similar covariate distributions [33]. Despite this fact, propensity score matching including among other variables baseline WOMAC scores as matching factors may reduce variance of outcome measures and therefore probably increase the power of the study further if the propensity score is included as covariate in the statistical evaluation model. However, it is difficult to quantify this effect and thus we conservatively calculated the sample size obtained for the parallel group design with cluster effect as described in the preceding paragraph.

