**Methods/design:**

This is a controlled study in the context of health services research. The study population consists of *n* = 1400 subjects with hip or knee osteoarthritis. The intervention group will be recruited from participants of a country-wide health insurance offer for people with hip or knee osteoarthritis. Potential participants for the control group (ratio 10:1 (control vs. intervention) will be filtered out from the insurance data base according to pre-defined matching criteria and asked by letter for their participation. The final statistical twins from the responders (1:1) will be determined via propensity score matching. The progressive training intervention comprises 8 supervised group sessions, supplemented by home exercises (2/week over 11 weeks). Exercises include mobilization, strengthening and training of postural control. Primary outcomes are pain and function measured with the WOMAC Index immediately after the intervention period. Among other things, health related quality of life, self-efficacy, cost utility and safety will be evaluated as secondary outcomes. Participants will be followed up 6, 12 and 24 month after baseline.

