The finally defined controls and cases will be included into a linear model with the propensity score as covariate. Additionally, we will use models for longitudinal data using each measurement point (instead of only t0 and t3 for the primary analysis). The level of significance will be 0.025 for primary endpoints. Secondary endpoints will be analyzed analogously without claiming confirmatory interpretation of *p*-values.

Descriptive analysis will include absolute and percentage frequencies for categorical variables, means, medians, standard deviations, quartiles and ranges for quantitative variables and medians, quartiles and ranges for ordinal variables. For the main results, two-sided 95 % confidence limits will be given additionally to significance tests. For percentages exact confidence interval for proportions based on the binomial distribution will be given.

Exploratory, prognostic factors will be analyzed using multiple regression models (linear regression) to identify potential responders to the training.

Correlation analyses will use Pearson product moment correlation coefficient (normally distributed variables) and Spearman correlation (non-normally distributed variables).

The primary analysis will be done on the full set of patients recruited in consideration of the exclusion criteria “limited pain and impairment in physical function” (WOMAC Index subscales pain and physical function with values below 15) except for patients refusing consent during the study and obviously wrongly diagnosed patients. A secondary analysis will be done using the full set of eligible and included patients irrespective of their limitations in pain and physical function at baseline (t0). This secondary analysis will only claim confirmatory interpretation of p-values if the primary analysis is able to detect group differences in a statistical manner. Otherwise the secondary analysis will be done in an explorative manner.

Missing values will be imputed using multiple imputation approaches, complete case and last observation forward analysis will be performed as a sensitivity analysis. No interim analysis, except for administrative purposes will be performed. All statistical analysis will be done using the software SPSS and R in the newest release.

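### Fixed Bonferroni at 0.025 for each primary endpoint is valid but gives up some power that Holm's procedure would recover, provided the gate to the full-set analysis is tightened as well

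*Protocol article*

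**What the plan says.** The family has two members: "Primary outcomes are pain and function measured with the WOMAC Index immediately after the intervention period". Under Sample size the protocol explains that "we want to test the two endpoints (pain and physical function) simultaneously and without hierarchical order", and for that reason "we choose a level of significance of 0.025 (two-sided, Bonferroni correction) and a power of 0.90". The section on matching procedures and statistical analysis of clinical endpoints carries the same rule into the analysis: "The level of significance will be 0.025 for primary endpoints". Neither place mentions a step-down.

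Two further statements in the analysis section matter here.
- For the main results, two-sided 95% "confidence limits will be given additionally to significance tests".
- A secondary analysis adds back the patients with low baseline WOMAC scores (the full set). It may claim confirmatory p-values once the primary analysis has detected group differences. The text does not say whether one endpoint is enough to open this gate.

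**The concern.** Under fixed Bonferroni each endpoint is judged at 0.025 whatever happens to the other. Holm tests the smaller p-value at 0.025 and, if that is rejected, the other at 0.05. It needs no pre-set order, so it respects the stated reason for choosing Bonferroni.

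The primary aim under Study purpose names less pain and better function. The 90% power is per endpoint, so the chance of confirming both is lower. What is at stake is the case where one subscale is clearly significant and the other has a p-value between 0.025 and 0.05. Holm would confirm the second; the present rule would not.

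**Working it through.** **Inputs from the protocol.** Effect size: "we finally assume an effect size of ES = 0.3". Two-sided 0.025 per endpoint, power 0.90, 20% non-finishers, about four study participants per course, intraclass correlation 0.33, 700 per arm. The correlation ρ between the two endpoints is not given; I assume 0.5 to 0.85 and equal effects on both.

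**The plan's own figure.** n = 2(z₀.₉₈₇₅ + z₀.₉₀)²/0.3² = 2(2.2414 + 1.2816)²/0.09 = 275.8, so 276 by the normal approximation. The t test has power 0.8999 at 277 and 0.9010 at 278, so the stated 278 reproduces. Dropout: 278/0.8 = 347.5, so 348, given as 350. Design effect: 1 + 3 × 0.33 = 1.99, hence about 700. Completers: 700 × 0.8 = 560 per arm.

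**Formulas.** Let δ be the mean of each test statistic, c₁ = 2.2414 (level 0.025) and c₂ = 1.9600 (level 0.05). Let B(a, b) be the bivariate normal probability that one statistic exceeds a and the other exceeds b.
- Power per endpoint, Bonferroni: Φ(δ − c₁)
- Both endpoints, Bonferroni: B(c₁, c₁)
- Both endpoints, Holm: 2B(c₁, c₂) − B(c₁, c₁)
- At least one endpoint, either procedure: 2Φ(δ − c₁) − B(c₁, c₁)

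**Values of δ.**
- No clustering: 0.3 × √(560/2) = 5.020
- Inflation of 2 in the intervention arm only: 0.3/√(2/560 + 1/560) = 4.099
- Inflation of 2 in both arms: 0.3/√(2/560 + 2/560) = 3.550
- The Discussion's 80% power: 2.2414 + 0.8416 = 3.083

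| Scenario | Power per endpoint, Bonferroni | Both, Bonferroni → Holm (ρ = 0.7) | Gain in both, ρ 0.5 to 0.85 (points) |
|---|---|---|---|
| No clustering | 99.7% | 99.5% → 99.8% | 0.3 to 0.2 |
| Inflation 2, intervention arm | 96.8% | 94.8% → 97.1% | 2.6 to 1.9 |
| Inflation 2, both arms | 90.5% | 85.3% → 90.6% | 5.9 to 4.4 |
| 80% power as stated | 80.0% | 71.3% → 79.4% | 9.1 to 7.1 |

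The last row implies heavier clustering than the plan's factor of 2. At 560 completers and effect size 0.3 it needs an inflation of (5.020/3.083)² ≈ 2.65 in both arms.

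**Error within the two-endpoint family.** By simulation, with both nulls true, the family error is the same under both procedures: 4.9%, 4.7% and 4.0% at ρ = 0, 0.5 and 0.8. With one null true (278 per group, effect size 0.3 on the other endpoint), Holm's false-rejection rate is 4.7%, 4.5% and 4.1%.

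**Error once the full-set analysis is added.** Suppose function has no effect in either set, pain is rejected with certainty, and one rejection opens the gate. Let the primary set be 70% to 90% of the full set (assumed), so the two function statistics correlate at the square root of that share. The chance of a false claim on function is:
- Bonferroni, full set at 0.025: 3.3% to 3.9%
- Holm, full set at 0.025: about 5.3% to 6%
- Holm, full set at 0.05: 6.5% to 7.6%

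Holm gives the rejected endpoint's 0.025 to the other primary endpoint. An unchanged gate would spend it again in the full set.

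**The case against.** The strongest case for leaving the plan alone is that nothing in it is wrong. Bonferroni controls the error, a reason is given, the sample size is right for it, and both sections use the same level. The protocol powers each endpoint separately and nowhere makes success depend on both. All of that stands, so this is a matter of efficiency.

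A reader might infer a routine loss of 5 to 9 points. The documents do not support that as a general figure. The inflation factor is stated for the intervention, and controls attend no course, so the 2 to 3 point scenario is the closest to the plan's own wording. The 80% figure is tied to unfavourably high clustering, and the Discussion itself expects more than 90%.

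A reader might also infer that a one-sentence change is free. It is not: the calculation above shows that, with an unchanged gate, the overall error can exceed 5%.

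The interval argument cuts both ways. The planned 95% limits do not match tests at 0.025, so Bonferroni's advantage of simple matching intervals is not being used. It could be used, by reporting 97.5% limits. Holm offers no equally simple counterpart.

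**Conclusion.** The point holds as a cheap, optional improvement. Holm confirms both endpoints more often at the same two-sided 5% error for the pair, and leaves the chance of at least one significant endpoint unchanged. On the plan's inputs the gain is small unless clustering is strong. Its size depends on the assumed correlation and on equal effects; that Holm is never less powerful than Bonferroni depends on neither.

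The documents do not support reading this as a flaw in the Bonferroni rule, an error in the sample size, or a sign that the trial is underpowered for its aim.

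**What to change.** In the analysis section, before any follow-up data are analysed:
1. Replace the fixed 0.025 by the Holm procedure across WOMAC pain and physical function at two-sided family-wise 0.05.
2. State that the full-set analysis is confirmatory only if both primary endpoints are rejected. This also settles what now opens the gate.
3. Keep the sample size as calculated at 0.025, which is conservative under Holm.

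The cost is about two sentences, with no extra patients or data. There are two downsides: the full-set analysis becomes confirmatory less often than if one endpoint were enough, and there are no simple simultaneous confidence intervals that match Holm, so the 95% limits should be labelled as unadjusted.

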#### Matching procedures and statistical analysis of clinical endpoints

The matching procedure for the statistical twins of the control group (CO) will be conducted as followed: ten statistical controls for each participant of the intervention group will be selected from the insurance data base according to the matching criteria displayed in Table 5. If it is not possible to select ten matches for a subject of the intervention group according to the criteria and tolerances displayed in Table 5, the tolerance will be extended in an iterative manner (steps of 100 Euro or 1 day respectively) until ten controls can be extracted from the data base.

**Table 5 Tab5:** Matching criteria to extract 10 controls for each participant of the intervention

Criteria	Tolerance
Co-morbidity: Quantity of hierarchical ordered morbidity groups in the previous year	0
Osteoarthritis of the hip or knee joint in the previous year: yes/no	0
Participation in a special general practitioner care program (“Hausarztzentrierte Versorgung”): yes/no	0
Routine data: Age (years), gender, type of insurance (compulsorily insured, family insured, pensioner, unemployed), complexity of work (from 1 = low to 4 = high), level of education (1 = no graduation to 4 = High School), highest level of educational attainment (from 1 = no qualification to 6 = doctoral degree), contractual form (permanent/fixed term contract, full time/part time)	0
Joint replacement in the last 24 month prior t0 at the hip and/or knee joint(s): yes/no	0
Sum of unspecific health care costs (overall costs) in the last 24 month prior t0: Sick-pay, hospital costs, out-patient costs, costs related to periods of disability and costs related to drugs, physical modalities and adjuvants.	+/− 100 EUR
Sum of unspecific health care costs (overall costs) in the last 6 month prior t0 (tm6): Sick-pay, hospital costs, out-patient costs, costs related to periods of disability and costs related to drugs, physical modalities and adjuvants.	+/− 100 EUR
Sum of specific diagnosis (hip/knee OA) related health care costs in the last 24 month prior t0: Sick-pay, hospital costs, out-patient costs, costs related to periods of disability and costs related to disease related drugs, physical modalities and adjuvants such as walkers, cranks or orthotics.	+/− 100 EUR
Sum of specific diagnosis (hip/knee OA) related health care costs in the last 6 month prior t0 (tm6): Sick-pay, hospital costs, out-patient costs, costs related to periods of disability and costs related to disease related drugs, physical modalities and adjuvants such as walkers, cranks or orthotics.	+/− 100 EUR
Disability days in the last 24 month prior t0 (tm24)	+/− 1 Day
Disability days in the last 6 month prior t0 (tm6)	+/− 1 Day
Specific disability days (hip/knee OA) days in the last 24 month prior t0 (tm24)	+/− 1 Day
Specific disability days (hip/knee OA) in the last 6 month prior t0 (tm6)	+/− 1 Day

Legend: a tolerance of “0” is equal to complete agreement, i.e. for age in years. Matching criteria are derived from the insurance data base

The matching process for the identification of statistical controls (CO) for each subject of the intervention group will be permuted in blocks: The matching procedure will be conducted quarterly until the number of needed subjects is reached.

Selected subjects will be asked for study participation (see section recruiting). The final statistical twins for each participant (1:1 matching) will be selected from all eligible responders. As a primary criterion, twins must be identical with regard to site(s) of OA (hip, knee or both). The following independent variables of the self-administered questionnaires (SAQ) and insurance data base (IDB) will then be used as input variables for the logistic regression of the PSM:Socio-demographic data at t0: age and gender (SAQ)Co-morbidity: Quantity of hierarchical ordered morbidity groups in the previous year (IDB)Osteoarthritis of the hip or knee in the previous year (IDB)WOMAC Index subscale pain at t0 (SAQ).WOMAC Index subscale physical functioning at t0 (SAQ).Quality Adjusted Life Years at t0 via VR-6D (SAQ).Body mass index at t0 (SAQ).Joint replacement hip and/or knee joint(s) at t0 (SAQ).General Self-Efficacy scale GSE at t0 (SAQ)Habitual physical and sports activity status at t0Participation in health activity programs (i.e. walking courses) at t0

If there are any cost/disability day categories, in which the standard mean differences after matching are above 0.05, a new matching will be conducted with these cost/disability day categories as matching variables in addition. No follow-up data will be analyzed prior to the final definition of the statistical twin of the CO for a given IG patient.

The finally defined controls and cases will be included into a linear model with the propensity score as covariate. Additionally, we will use models for longitudinal data using each measurement point (instead of only t0 and t3 for the primary analysis). The level of significance will be 0.025 for primary endpoints. Secondary endpoints will be analyzed analogously without claiming confirmatory interpretation of *p*-values.

Descriptive analysis will include absolute and percentage frequencies for categorical variables, means, medians, standard deviations, quartiles and ranges for quantitative variables and medians, quartiles and ranges for ordinal variables. For the main results, two-sided 95 % confidence limits will be given additionally to significance tests. For percentages exact confidence interval for proportions based on the binomial distribution will be given.

Exploratory, prognostic factors will be analyzed using multiple regression models (linear regression) to identify potential responders to the training.

Correlation analyses will use Pearson product moment correlation coefficient (normally distributed variables) and Spearman correlation (non-normally distributed variables).

The primary analysis will be done on the full set of patients recruited in consideration of the exclusion criteria “limited pain and impairment in physical function” (WOMAC Index subscales pain and physical function with values below 15) except for patients refusing consent during the study and obviously wrongly diagnosed patients. A secondary analysis will be done using the full set of eligible and included patients irrespective of their limitations in pain and physical function at baseline (t0). This secondary analysis will only claim confirmatory interpretation of p-values if the primary analysis is able to detect group differences in a statistical manner. Otherwise the secondary analysis will be done in an explorative manner.

Missing values will be imputed using multiple imputation approaches, complete case and last observation forward analysis will be performed as a sensitivity analysis. No interim analysis, except for administrative purposes will be performed. All statistical analysis will be done using the software SPSS and R in the newest release.

